## Abstract

**Background:**

Around 150,000 people each year attend hospitals in England due to self-harm, many of them more than once. Over 5,000 people die by suicide each year in the UK, a quarter of them having attended hospital in the previous year because of self-harm. Self-harm is a major identifiable risk factor for suicide. People receive variable care at hospital; many are not assessed for their psychological needs and little psychological therapy is offered. Despite its frequent occurrence, we have no clear research evidence about how to reduce the repetition of self-harm. Some people who have self-harmed show less active ways of solving problems, and brief problem-solving therapies are considered the most promising psychological treatments.

**Methods/Design:**

This is a pragmatic, individually randomised, controlled, feasibility study comparing interpersonal problem-solving therapy plus treatment-as-usual with treatment-as-usual alone, for adults attending a general hospital following self-harm. A total of 60 participants will be randomised equally between the treatment arms, which will be balanced with respect to the type of most recent self-harm event, number of previous self-harm events, gender and age. Feasibility objectives are as follows: a) To establish and field test procedures for implementing the problem-solving intervention; b) To determine the feasibility and best method of participant recruitment and follow up; c) To assess therapeutic delivery; d) To assess the feasibility of obtaining the definitive trial’s primary and secondary outcomes; e) To assess the perceived burden and acceptability of obtaining the trial’s self-reported outcome data; f) To inform the sample size calculation for the definitive trial.

**Discussion:**

The results of this feasibility study will be used to determine the appropriateness of proceeding to a definitive trial and will allow us to design an achievable trial of interpersonal problem-solving therapy for adults who self-harm.

**Trial registration:**

Current Controlled Trials (ISRCTN54036115)

## Background

Self-harm is usually defined in UK health services as intentional self-poisoning or self-injury, irrespective of motivation [1]. It has been a major health problem in the UK for 50 years. Rates have never been collected for England nationally, but estimates based on the UK Department of Health funded multicentre monitoring project (in the cities of Manchester, Oxford and Derby) suggest that current rates are a little below their highest ever levels seen in 2003: rates in males are around 350 and in females 480 per 100,000 per annum [2]. Hospitals in England deal with an estimated 220,000 episodes undertaken by 150,000 people each year [3]. Around 80% of these hospital episodes are self-poisoning (usually medicines overdose) while 15 to 20% are injuries (most commonly self-cutting). People who self-harm are high users of health and social care services [4] and two-thirds are aged under 35 years [3]. Time-to-event curves based on 11,000 consecutive self-harm episodes in Leeds between October 2004 and September 2007 show evidence for a difference in repetition rates of self-harm between age groups. Those aged between 30 and 59 years are at the highest risk of repetition whilst those aged over 60 are at a reduced risk compared to other age groups (unpublished data, [name], [name], [name]). Self-harm has a strong link with suicide: 7 per 1000 people die by suicide in the year after attending hospital with a non-fatal episode of self-harm (60 times higher than the general population risk); by 15 years after self-harm, as many as 30 per 1000 people will have died by suicide [1,5-7]. A quarter of the 5000 to 6000 annual suicides in the UK are preceded by a hospital visit due to non-fatal self-harm in the previous year [8]: it is a major identifiable risk factor for suicide. There is also an excess of premature deaths in those with a history of self-harm from natural causes and accidents [9-11], with many life years lost - particularly among young people. Non-fatal repetition is common (1-year repetition rates are 16% or more) [5] and is associated with distress and unresolved interpersonal problems [12].

UK hospital services for people who self-harm are inconsistent; only around half of patients receive a basic assessment of their state of mind and social circumstances before discharge from emergency departments or medical wards [13]. Unfortunately there is no consensus that intervention at this stage is worthwhile and so therapy is not routinely offered. Despite more than 40 randomised controlled trials in self-harm, a Cochrane review [14] found only small and methodologically poor trials had been previously conducted and no clear evidence that intervention reduces repetition. The review suggested potential benefit from small trials involving problem-solving therapy, a brief and focused psychological intervention with a proven benefit in depression that is known to reduce hopelessness and suicidal ideation [15], concluding that ‘larger trials are badly needed’. A comprehensive American review [16] similarly judged the existing studies to have three main limitations: lack of power, poor description of standard care and inconsistent age ranges across studies. It further stated that the ‘trends suggested incremental benefits from some interventions (in particular, problem-solving therapy for people aged 15 or older)’. It is therefore not surprising that the UK’s National Institute for Health and Clinical Excellence (NICE) guideline on self-harm reported that, as far as psychological intervention is concerned, there was ‘insufficient evidence to make any positive or negative recommendations’ [17], a view echoed in a 2010 report from the UK Royal College of Psychiatrists [18].

Trial evidence that post-dates these reviews adds little to guide routine practice. One UK multicentre randomised controlled trial (RCT) of ‘manual-assisted cognitive behavioural therapy’ [19] failed to find any clear benefit from the new treatment, or any indications of how to steer delivery of interventions for self-harm in the UK National Health Service (NHS). It was, however, underpowered for the following reasons: it was restricted to a study sample unrepresentative of the population of people attending hospital because of self-harm; many of the participants in the active treatment arm did not receive the intervention; and the intervention itself was not, on theoretical or empirical grounds, adequately designed for use in self-harm. Two American trials showed benefits with highly selected participants and intensive forms of expert therapy: 1) ten sessions of cognitive therapy reduced non-fatal repetition in people judged to have made suicide attempts [20] and 2) intensive dialectical behaviour therapy reduced repetition of self-harm in young women with a diagnosis of borderline personality disorder [21]. Costs, in terms of time in therapy and therapist expertise, preclude the widespread use of either of these interventions for subgroups of patients in UK hospitals, and the cost-effectiveness of such interventions for self-harm is unknown. A New Zealand trial of problem-solving therapy found that it was effective in preventing repeat presentation to hospital due to self-harm at one year in those who repeat self-harm, but not in those whose index admission was their first episode [22]. In its guidance on the longer term management of self harm, NICE continues to emphasise the need for further research into the modality, duration, and extent of benefit for therapy interventions, carried out in ‘real-world’ clinical settings [23]. A future definitive RCT is planned, however this feasibility study is first required to inform the design of such a large trial. The projected definitive trial will test the hypothesis that brief problem-solving therapy, when compared with treatment as usual, will reduce repetition (whether fatal or non-fatal) of self-harm; the present feasibility study is not designed to test a hypothesis but to pave the way for the successful undertaking of a definitive trial.

## Methods/Design

### Aims and objectives

MIDSHIPS is a pragmatic, multi-centre, individually randomised, controlled feasibility study, designed to determine the practicability of undertaking a definitive RCT of interpersonal problem-solving therapy plus treatment-as-usual (PST + TAU), compared with treatment-as-usual only (TAU), for adults who attend a general hospital due to self-harm.

Objectives relate to the feasibility of implementing a definitive RCT. The content of the manual and procedures for training therapists in PST, recruiting and training therapists, assessing therapist competence, and determining procedures for therapist supervision must be established. The evaluation of processes to screen patients for eligibility, determining feasibility and best methods of recruitment, and establishing participant uptake and retention during follow up must also be examined. It is important to establish the retention rate in therapy, methods for measuring adherence to PST, and characterising the range of TAU offered and attended. It is also essential to assess the feasibility of collecting the primary outcome for the definitive trial (repeat attendance at hospital following self-harm) from hospital records, establishing likelihood of obtaining the main trial’s secondary outcomes (Short Form 36, healthcare resource use, self-reported self-harm) via postal administration or telephone interviews, and assessing the burden and acceptability of self-reported outcome data. Finally, the variability of outcomes must be estimated in order to inform the sample size calculation for a definitive trial.

### Setting

A total of 60 participants (30 in each arm) will be recruited following attendance at a general hospital as a result of self-harm. The three hospitals involved are those whose mental health services are provided by the Leeds and York Partnership NHS Foundation Trust (LYPFT). People not approached to take part in the study can self-refer, provided that they have recently attended the general hospital due to self-harm, through the provision of information about the trial at the Leeds Survivor Led Crisis Service.

### Participants

#### *Inclusion criteria*

To be included in the study, participants must meet the following eligibility criteria: a) be aged 18 years or over; b) have attended the emergency department or been admitted to a general hospital as a consequence of self-harm (intentional self-poisoning or self-injury irrespective of motivation) within the last six weeks; c) not already be participating in the MIDSHIPS trial; and d) where the presenting episode is due to alcohol or recreational drugs, the participant explicitly stated that they were intending self-harm by use of alcohol or recreational drugs.

#### *Exclusion criteria*

Participants will be ineligible for the study if they meet any of the following criteria: a) they are involved in another research project or clinical service involving a conflicting intervention such as the Personality Disorder service; b) they do not live in the LYPFT catchment area; c) they do not provide fully informed written consent; d) they lack the capacity to comply with trial requirements; e) they are not sufficiently proficient in English to contribute to the data collection required for the research; f) there is a perceived risk of violence towards the therapist or researcher; and g) the researcher is unable to contact the participant within eight weeks following the self-harm event.

### Recruitment

Patients attending hospital following self-harm receive a mental health assessment by the clinical staff following physical treatment, during which formal screening for eligibility occurs. Eligible patients are given the MIDSHIPS study card, which briefly describes the study, and are asked to provide written permission for a researcher to contact them. For those who self-refer to the study via the Leeds Survivor Led Crisis Service, the clinical staff review completed study cards, determine eligibility and if appropriate, provide the researcher with the patient’s details.

Following referral, the researcher telephones those who have consented to be contacted to explain the study in more detail and establish full eligibility. The MIDSHIPS participant information sheet is sent to those eligible, who then have at least 24 hours to read and digest the information before the baseline visit, at which written informed consent is obtained.

To inform generalisability of the study results, screening logs are completed for all people screened for entry into MIDSHIPS; for those screened and not recruited, anonymised data are collected on age, gender, reasons for ineligibility and reasons for non-randomisation.

### Randomisation

Consenting participants are randomised on a 1:1 basis to receive PST + TAU or TAU alone via the Clinical Trials Research Unit’s (CTRU) automated 24-hour randomisation system. A computer generated minimisation algorithm incorporating a random element is used to ensure the treatment arms are well balanced for the following characteristics: a) number of previous episodes of self-harm leading to hospital attendance, prior to baseline assessment (one, more than one), b) type of most recent episode (self-poisoning, self-injury, both injury and poisoning combined), c) gender (male, female) and d) age (<30, 30 to 59, ≥60). Participants and therapists are, of necessity, aware of treatment allocation, but the collection of outcome data by researchers is undertaken blind to this knowledge.

### Intervention

#### *Treatment-as-usual*

Treatment following self-harm varies and may involve referral to a multi-disciplinary mental health team, referral to a mental health crisis team and recommendation for attendance at other services including alcohol and drug treatment centres. In many instances in UK current clinical practice, no aftercare is offered, and the only action to follow discharge from hospital is a letter sent to the general practitioner summarising the episode. TAU for randomised participants is recorded in both arms of the study. In order to avoid contamination across the two arms of the trial, we ensured that the therapists did not participate in the TAU activity.

#### *Interpersonal problem-solving therapy*

Overwhelming problems can have an adverse effect on people’s existing problem-solving skills, such that impulsive responding and incomplete solutions may become more likely. In people who have self-harmed, the result may be less active problem-solving, reliance on the actions of others, waiting for resolution, and limited generation of alternative solutions – all of which reinforce existing negative beliefs about self and self-blame. Interpersonal PST is an established, brief, focused, and readily-learned psychotherapy with a proven benefit for depression and is known to reduce hopelessness and suicidal ideation [15]. In a New Zealand RCT of PST, seeking to reduce hopelessness and repetition of self-harm [22], the research team successfully amended the therapy to fit the needs of their patients who had self-harmed. This manual, along with training processes and client workbooks, has been adapted for UK NHS use. Trial therapists have been recruited, as a part-time secondment, from the clinical mental health service in Leeds. The target groups of staff for this recruitment were experienced but not senior practitioners in mental health nursing, occupational therapy, or social work. Training in problem-solving therapy has been delivered as a three-day course followed up with supervision sessions with a senior psychiatrist with experience in self-harm management and problem-solving therapy ([name]).

Participants randomised to PST receive up to six one-hour weekly individual sessions delivered one-to-one by the trial therapists. Sessions focus on the identification of current problems and a structured psycho-educative approach to problem-solving. In addition, participants are offered an optional ‘booster’ session, approximately six to eight weeks following the end of therapy.

The therapists receive regular supervision in the use of the problem-solving therapy as part of the research procedure, and participants in the trial remain patients of the clinical service (the single UK National Health Service Trust) from which they are recruited. The therapists can urgently refer any clinical emergencies or concerns about the participant’s mental state to the standard clinical service, to be dealt with promptly through the existing arrangements for urgent assessment and care.

### Data collection

At baseline, the researcher collects details of the index self-harm event (the event leading to hospital attendance which prompted entry into the study), self-harm history, current physical and mental health, social and medical history, current psychotropic medications, education, and employment details. At baseline and at three and six months post-randomisation, the participant is asked to complete the Short-Form 36 [24] and a trial-specific questionnaire about the use of health and social care resources, private expenses, and lost productivity. Self-reported self-harm events are also collected at both follow up time points. All follow up outcome data are collected by post or by telephone following non-response to postal reminders. Participants are sent £10 shopping vouchers with each questionnaire mailing to thank them for their time. On receipt of the six-month questionnaires the researcher telephones the participant to assess the perceived burden and acceptability of the task of completing the research questionnaires, and obtains additional information on treatment received and current psychotropic medications via a trial-specific, semi-structured interview schedule. A further £10 shopping voucher is sent following this interview.

Data relating to therapy are collected directly from therapists and case notes by UK Research Network staff with support from CTRU. These data relate to therapy (type, dates, number of sessions offered and attended and contact between sessions), therapist supervision, referrals to and attendance at other services (including the mental health crisis team and alcohol and drug treatment centres), and psychotropic medication details. Admissions to or attendance at hospital and all-cause mortality are collected from hospital records by the researcher.

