### Outcomes

To establish the problem-solving intervention this requires a finalised training manual and successfully implemented procedures for recruiting and training therapists, in addition to having an agreed and field tested method for assessing therapist competence and recording supervision.

Outcomes relating to recruitment methods, uptake and follow up include screening, eligibility, consent, and randomisation rates together with reasons for non-participation and participant retention during follow-up.

To determine whether therapeutic delivery is successful we will examine attendance, therapy completion rates, and reasons for early dropout together with adherence to therapy by participant and therapist. The range of TAU pathways across treatment arms will also be investigated.

Outcomes related to follow up data collection will include the proportion of participants with self-harm repetition data - whether non-fatal or fatal (suicide), a comparison of self-reported self-harm with data collected from hospital records , the proportion of participants with self-reported outcome data and an assessment of missing data.

Statistical outcomes which will inform the sample size calculation for a definitive trial include the repetition of and time to self-harm leading to hospital attendance within six months post-randomisation, and the difference between arms, the variability of self-reported outcomes at follow up and the difference in self-reported outcomes at follow up.

A qualitative summary of burden and acceptability of self-reported outcomes will also be achieved by examining the participant follow-up interviews.

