### Sample size

As this is a feasibility study and effectiveness is not being evaluated, formal power calculations are not appropriate. It is recommended that feasibility studies recruit a minimum of 30 participants per arm to allow for the investigation of parameters and outcomes for a definitive RCT [25]. We therefore plan to recruit 60 participants in total, randomised equally between TAU and PST + TAU.

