Self-reported outcome data completion will be assessed by summarising response rates at baseline and follow up. The level of missing data (at the individual item level and for entire outcome measures) together with qualitative participant interview data will inform the appropriateness of the tools and the level of burden for the definitive trial. An exploratory cost-effectiveness analysis (using SF36 and the health and social care resource use questionnaire) will be produced, together with indicative costs for the interventions.

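### The burden and acceptability interview is triggered by receipt of the six-month questionnaires, so participants who supply no six-month data are not asked and the summary for objective (e) is likely to favour acceptability

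*Protocol article*

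**What the plan says.** The Abstract lists six feasibility objectives. Objective (e) is: "To assess the perceived burden and acceptability of obtaining the trial’s self-reported outcome data".

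The direct enquiry that serves it is a telephone interview described under Data collection: "On receipt of the six-month questionnaires the researcher telephones the participant to assess the perceived burden and acceptability" of completing the questionnaires. The Outcomes section draws its summary from that source: "A qualitative summary of burden and acceptability of self-reported outcomes will also be achieved by examining the participant follow-up interviews". No burden interview is described at three months, and none for people who return nothing at six months.

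Three other statements bear on the point:

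- Under Statistical analysis, missing data, counted by item and by whole measure, "together with qualitative participant interview data will inform the appropriateness of the tools and the level of burden for the definitive trial".
- Under Data collection, postal non-responders have a second route: "All follow up outcome data are collected by post or by telephone following non-response to postal reminders".
- The same interview asks for additional information on treatment received and psychotropic medication. The next paragraph of Data collection also takes therapy, referral and medication data from therapists and case notes.

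A £10 voucher goes out with each questionnaire mailing, and a further £10 follows the interview.

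**The concern.** Receipt of the questionnaires is the entry condition for an interview about how hard they were to complete. Those who found the task too long, too upsetting or too intrusive are among the people most likely to send nothing back, and under this rule nobody asks them. That is selection on the thing being measured.

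A feasibility study has particular reason to hear from this group, because their reasons show what to change before the definitive trial: a shorter instrument, another mode, different timing. A summary drawn from completers can leave those themes out, and the plan uses the interview material in judging whether the tools suit the definitive trial. The matter affects one named objective. It does not touch the collection of repeat self-harm from hospital records, which is the primary outcome intended for the definitive trial.

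**Working it through.** **The plan's own figure.** The only design number is the sample size: "We therefore plan to recruit 60 participants in total, randomised equally between TAU and PST + TAU". Two arms of 30 give 2 × 30 = 60, which reproduces. The documents state no questionnaire return rate and no acceptability figure, so there is nothing further to recompute.

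**Who is asked, reading the sections together.**

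| Participant at six months | Counted in the missing-data assessment? | Asked about burden in the interview? |
|---|---|---|
| Returns by post | Yes, as a responder, with any missing items | Yes |
| Fails by post, completes by telephone | Yes, as a responder, with any missing items | Not stated: telephone completion may or may not count as receipt |
| Supplies nothing by either route | Yes, as wholly missing measures | No, as written |

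The third row is the settled part of the point and the second is an ambiguity. The middle column holds counts. A wholly missing measure looks the same whether the person found it too burdensome, moved house, was unwell or lost contact. The Outcomes section lists reasons for non-participation and for early dropout from therapy, but no reasons for questionnaire non-return.

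**How much it could matter (illustration only).** Let r be the proportion who supply six-month data and are interviewed, a the proportion of these who find the task acceptable, and b the same proportion among the rest. Then

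overall acceptability = r·a + (1 − r)·b, and interview figure minus overall = (1 − r)(a − b).

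The values of r, a and b are all assumed. With N = 60 and a = 0.80:

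| r (interviewed / not) | b = 0 | b = 0.25 | b = 0.80 | b = 1 |
|---|---|---|---|---|
| 0.9 (54 / 6) | 0.720 | 0.745 | 0.80 | 0.82 |
| 0.8 (48 / 12) | 0.640 | 0.690 | 0.80 | 0.84 |
| 0.7 (42 / 18) | 0.560 | 0.635 | 0.80 | 0.86 |
| 0.5 (30 / 30) | 0.400 | 0.525 | 0.80 | 0.90 |

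One cell in full: r = 0.8, b = 0.25 gives (48 × 0.80 + 12 × 0.25)/60 = (38.4 + 3.0)/60 = 0.69, so the interviews would show 0.80 and the gap is 0.2 × 0.55 = 0.11.

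The gap is zero when non-returners think as returners do, and its sign reverses if they find the task more acceptable. The direction thus rests on the premise that burden makes return less likely. That premise is reasonable but is not shown in the documents.

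**The case against.** The strongest case on the other side has four parts.

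*Burden is not judged from interviews alone.* This is correct. A reader might infer that the interview is the sole evidence, but missing items and missing measures are used with it, so non-completion does count. What remains is that counts carry no reasons.

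*Postal non-responders are telephoned.* Also correct. A reader might infer that every postal non-responder goes unasked, and the text does not support that. Data given by telephone may well be treated as receipt, in which case the excluded group shrinks to those who fail both routes, who are also the hardest to interview. The text leaves this open, and a rule that can be read both ways should be settled.

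*The output is a qualitative summary, not a prevalence.* This stands against any numerical claim of bias. It does not remove the selection: a summary from completers can still miss what non-completers would have said.

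*This is a condensed article.* Call scripts and the recording of reasons for non-return could be in the full protocol, and their absence here is no finding. The trigger itself, however, is stated, and the point rests on that.

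One further inference should be resisted: that treatment-received and medication data are missing for non-responders because the same interview collects them. The article calls what the interview adds supplementary, and it takes therapy, referral and medication data from therapists and case notes whether or not a questionnaire comes back. Non-responders lose a self-report supplement, not their treatment data.

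**Conclusion.** The point holds in a limited form. Tying the interview to receipt leaves those who supply no six-month data outside the direct enquiry into burden, and the position of telephone completers is unclear. The interview summary for objective (e) is therefore likely to lean towards acceptability.

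It would go too far to say that acceptability is overstated. Non-return has causes other than burden, and the size depends wholly on a return rate and on non-returner views that the documents do not give. Under the assumed inputs above, an interview figure of 80% could correspond to anything from 40% to 90% overall. That range shows how much is unknown; it is not an estimate. This is a cheap improvement to one feasibility objective, not a flaw that threatens the study.

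**What to change.** 1. Trigger the interview by time, at the close of the six-month reminder period, and offer it to every participant who has not withdrawn from contact, whether or not questionnaires have come back.
2. In the telephone follow-up call already planned for postal non-responders, add brief questions on burden and on the reason for not completing. This also settles the position of telephone completers.
3. Report the findings separately for postal responders, telephone responders and non-responders, with the interview response rate in each group and the questionnaire non-return rate alongside.

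Because the full interview asks about treatment received, and the Randomisation section has outcome data collected blind to allocation, keep the treatment questions out of the follow-up call and in the later interview.

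**Cost.** A few more calls and vouchers. If return were between 50% and 90%, as assumed above, the people added would number 6 to 30, so at most 6 × £10 = £60 to 30 × £10 = £300 in vouchers, and less if some cannot be reached. Prompt returners would be interviewed somewhat later after completing the forms. Some non-responders will remain unreachable, but the report would then show how many, instead of leaving them out by design.
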